**Fig. 3 Fig3:**
[figure not shown]
**a** Simple dressing application used in the control group. **b** PICO™ application used in the intervention group

**Fig. 4 Fig4:**
[figure not shown]
Schedule of assessment

Routine dressing changes will be performed once a day in the control group and twice a week in the intervention group. Additional dressing changes will be performed as needed during the postoperative hospital stay (i.e. when the dressing material is wet with discharge). If patients in the intervention group require dressing changes more than once a day during hospitalisation, we plan to replace the NPWT dressings with conventional dressings due to cost-effectiveness concerns, as NPWT dressing material is far more expensive than is conventional dressing material.

Outpatient follow-up after discharge will be scheduled twice a week until wound healing is judged as complete. Prophylactic antibiotics (second-generation cephalosporin) will be administered 1 h before surgery, and additional antibiotics will not be permitted unless there are signs of infection during the postoperative period.

### Sample size calculation

The target sample size will be 38 participants, as this will provide 80% power at the 5% (two-sided) level of significance to detect a 7-day reduction in the wound-healing period in the intervention group compared to that in the control group (superiority design, 19 ± 7 days vs 26 ± 7 days), with allowance for 10% attrition. The anticipated wound-healing period in the control group is based on data from a previous RCT that compared the healing times of the stoma reversal site between conventional linear closure and PSC [6]. We expect to screen approximately 44 patients for eligibility during the study period (*n* = 22 per year), based on the mean number of stoma reversal cases at our institution in the last 2 years. The length of the study period was decided with consideration of the expected screening number and a dropout rate of 20% (due to exclusion and refusal to consent).

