### Interventions

All participants will be randomised to either the intervention group or the control group, using a 1:1 ratio. The randomisation allocation will be generated using a computerised randomisation system and applied immediately after fascia occlusion to avoid a performance bias.

Stoma reversal will be performed using standard techniques, with the patient under either spinal or general endotracheal anaesthesia, and the bowel anastomosis will be either stapled or hand sewn at the discretion of the surgeon. After fascia closure, skin closure will be performed with the PSC method using absorbable monofilament suture material (2–0 Monocryl; Ethicon, Cincinnati, OH, USA), leaving an opening ≤ 0.5 cm (approximately). Subsequently, a simple, transparent, waterproof dressing will be applied to patients in the control group, and a PICO™ portable NPWT device (Smith & Nephew Healthcare, Hull, UK) dressing will be applied to patients in the intervention group (Fig. 3).

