### Trial status

This trial (protocol version 1.1) is in the ongoing recruitment phase, which started on 25 June 2019. The first participant was enrolled on 14 July 2019 and seven participants have been enrolled in the study as of 22 October 2019. The study will be completed on 30 June 2021.

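### The accrual figures do not reach the target: about 44 screened with a 20% loss gives about 35 randomised, 3 short of 38

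*Protocol article*

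**What the plan says.** The sample size section of the protocol article states: "The target sample size will be 38 participants". This is to give "80% power at the 5% (two-sided) level of significance to detect a 7-day reduction in the wound-healing period", under a "superiority design, 19 ± 7 days vs 26 ± 7 days", "with allowance for 10% attrition". Allocation is "using a 1:1 ratio" (Interventions).

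The same section then turns to feasibility: "We expect to screen approximately 44 patients for eligibility during the study period". The basis is a mean of 22 stoma reversal cases per year over the last two years. The study length is said to take account of that number and of "a dropout rate of 20% (due to exclusion and refusal to consent").

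The Trial status section gives 25 June 2019 as the start of recruitment and says: "The study will be completed on 30 June 2021". It also reports seven participants enrolled by 22 October 2019.

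**The concern.** The section gives a target to randomise, an expected number screened, and a loss rate between the two. These three should agree, because the planned study length is justified by them. They do not: the screening number reduced by the loss rate falls below the target.

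The two loss rates cannot be merged to close the gap. The 20% is defined as exclusion and refusal, so it acts before randomisation. The 10% attrition acts afterwards and is already inside the 38.

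At stake is whether the planned period can supply the sample on which the power statement depends. The Discussion answers the small-sample limitation by expressing confidence that power is adequate, and that confidence rests on 38 being reached.

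**Working it through.** **Inputs.** From Sample size calculation: difference 7 days, SD 7 days in each arm (standardised effect 1.0), two-sided 5%, 80% power, 10% attrition, about 44 screened (22 per year), 20% loss before randomisation. From Interventions: 1:1 allocation. From Trial status: 25 June 2019 to 30 June 2021.

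**1. Reproduce the 38.** With a two-sample t test (noncentral t), the smallest size giving at least 80% power is 17 per arm, with power 80.7%. That is 34 evaluable, and 34 / (1 − 0.10) = 37.8, rounded up to 38. The match is exact, so 38 is the number to randomise. The normal approximation would give 16 per arm, and 32 / 0.9 = 35.6, rounded up to 36.

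**2. Expected number randomised.**
- 44 × (1 − 0.20) = 35.2, so about 35, which is 3 short.
- To get 38 from 44, the loss could be at most 1 − 38/44 = 13.6%.
- At 20% loss, 38 / 0.80 = 47.5, so 48 must be screened. At 22 per year that takes 48 / 22 × 12 = 26.2 months.
- Reading 44 loosely does not help: 46 × 0.80 = 36.8, still short.

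**3. Check against the calendar.** The window is 736 days, and 736 / 365.25 = 2.015 years. At 22 per year that gives 44.3 screened, and 44.3 × 0.80 = 35.5 randomised. Completion must also include follow-up of the last patients to healing and the scar assessment at about 1 month. If 30 days are set aside for this, 706 / 365.25 × 22 × 0.80 = 34.0.

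**4. Power if recruitment stops at about 35.** With 10% attrition, 35 × 0.90 = 31.5, so 31 to 32 are evaluable.

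| Analysed (per arm) | t-test power | Normal approximation |
|---|---|---|
| 31 (16 + 15) | 76.7% | 79.5% |
| 32 (16 + 16) | 78.1% | 80.7% |
| 34 (17 + 17) | 80.7% | 83.0% |
| 35 (18 + 17), no attrition | 81.9% | 84.1% |

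**5. Observed accrual.** Seven enrolled in 119 days projects to 7 / 119 × 736 = 43.3 by the end date. The exact 95% Poisson interval for a count of 7 is 2.8 to 14.4. Scaled by 736 / 119, that is 17 to 89.

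**The case against.** The strongest reply is that the 80% is attached to 38 participants, not to a date, and is right for 38. That stands. A reader might infer that the sample size calculation is wrong, or that the true power is 77–78% instead of the stated 80%. The documents do not support either reading, because the 38 reproduces exactly.

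A reader might also infer that the trial will close on 30 June 2021 whatever number it has reached. The article gives that date as the completion date. It does not say that recruitment stops short of 38, nor that it will be extended. The loss of power is therefore conditional.

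The loss is also small and depends on several assumptions together. It needs the full 20% and the full 10%. If all 35 contribute an outcome to the intention-to-treat analysis, power exceeds 80%, and under the normal approximation the loss nearly vanishes. This too stands, with two qualifications: the t test is the method that yields 38 and is a planned test for the endpoints, and the 10% is the protocol's own allowance.

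Finally, early accrual projects to more than 38, even if the last 30 days are reserved for follow-up (7 / 119 × 706 = 41.5). Seven patients are too few to settle the matter in either direction, and the observed rate does not make the section's figures agree with each other.

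The study flowchart is not visible here and may show how the numbers were meant to run. It could not change what the text says.

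**Conclusion.** The inconsistency is real and lies between the target and the feasibility figures: about 35 randomised against 38. This follows from three numbers in one section and does not depend on any power method. The dates in Trial status do not close the gap.

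The consequence for power is conditional. Power of about 77–78%, some 2 to 3 points below the nominal 80%, arises only if recruitment stops so that the study completes on 30 June 2021, the 20% pre-randomisation loss occurs, and 10% attrition follows. The target, the effect assumption and the analysis are not affected. Severity is minor to moderate: the planned study length rests on a figure that does not add up, but the shortfall is about 3 patients.

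**What to change.** Amend the feasibility sentences in Sample size calculation, and the completion date if needed, in one of two ways.

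- **(a) Hold the target.** State that recruitment continues until 38 are randomised. Correct the expected screening number to about 48 (about 26 months at 22 per year, plus follow-up) and revise the completion date in Trial status. The cost is a completion date a few months later.
- **(b) Hold the date.** Keep 30 June 2021 and restate the expected size as about 35 randomised, 31 to 32 evaluable, with t-test power of about 77–78%. Qualify the Discussion's remark on adequate power to match. The cost is a slightly less favourable power figure.

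Either way, label the 20% as loss before randomisation, so that it is not confused with the 10% attrition after it.

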### Data collection and management

All data for this trial will be collected after obtaining informed consent from the participants 1 day before surgery. Paper case report forms will be used to record all baseline demographics and other data for each participant. Serial wound photographs will be taken by the investigators during dressing changes, from the immediate postoperative day to the discharge day during hospital stays, and at every visit to the outpatient clinic. The photographic data will be used to determine the degree of SSI and wound healing. All photographic data will be kept on file in an anonymised fashion, in the same manner as for the patient’s other data. All information acquired in this study will be anonymised through the assignment of a trial identification number, which will be used only for this trial and its research purposes, and will only be accessible to authorised persons. All data will be stored for 3 years from study completion.

All collected data and the participant’s safety will be monitored by a data and safety monitoring committee. The committee will meet once a year to monitor the study. Because of the proven safety of NPWT, the study is expected to be safe for the participants. Nevertheless, the investigators will monitor the participants for any severe adverse events related to the study treatment (e.g. a severe skin allergy due to the dressing materials) and will immediately report these to the data and safety monitoring committee. The investigators will change the study protocol according to the recommendations of the committee.

### Statistical analysis

No interim analyses will be conducted due to the small sample size of the study. All analyses of the primary/secondary endpoints will be conducted with the intention-to-treat population. A per-protocol analysis will be also performed for further comparisons. Normally distributed data will be examined using Student’s *t* test. Non-normally distributed data will be examined using the Mann–Whitney *U* test. The chi-square or Fisher’s exact test will be used to examine categorical variables. *p* < 0.05 will be considered statistically significant.

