### Endpoints

The primary endpoint will be the duration of wound healing, defined as the time to nearly complete epithelisation of the wound, without any discharge or SSI, which is similar to the definition used in the study by Uchino et al. [3]. The determination of the degree of wound healing will be made by the researcher and a single wound/ostomy-specialised nurse. Another colorectal surgeon (who will be blinded to the patient’s identity and treatment assignment) will also judge the extent of wound healing via photographs of the wound. Wound healing will be considered complete by the consensus of all three reviewers.

Secondary endpoints comprise the SSI rate, length of postoperative hospital stay, number of wound dressings and visits to the hospital for wound dressing after discharge, total cost of wound dressings, and patient and observer scar assessment scale (POSAS) scores [14]. The presence of an SSI will be decided by the researcher and wound/ostomy-specialised nurse, using the Center for Disease Control definition of SSI [15]. The evaluation of SSI will be performed using the same process as that for the assessment of wound healing. The POSAS will be completed at the outpatient clinic approximately 1 month after surgery.

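### Time to healing is tested by t or Mann-Whitney with no rule for patients lost unhealed, so the promised intention-to-treat analysis becomes, as written, one of about 34 completers

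*Protocol article*

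**What the plan says.** The Endpoints section gives the primary outcome (the sentence goes on to exclude surgical site infection): "The primary endpoint will be the duration of wound healing, defined as the time to nearly complete epithelisation of the wound, without any discharge or". This outcome exists only once healing has been observed. Under Interventions, "Outpatient follow-up after discharge will be scheduled twice a week until wound healing is judged as complete"; no last day of follow-up is given.

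The Sample size calculation section asks for 38 patients to detect 19 against 26 days (SD 7 in each arm) with 80% power at two-sided 5%, "with allowance for 10% attrition".

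The Statistical analysis section promises that "All analyses of the primary/secondary endpoints will be conducted with the intention-to-treat population", and adds: "A per-protocol analysis will be also performed for further comparisons". For continuous data it names two tests: "Normally distributed data will be examined using Student’s" t test, and "Non-normally distributed data will be examined using the Mann–Whitney" U test. It names no time-to-event method, no censoring rule, and no value or rank for a patient without a healing date.

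**The concern.** A patient last seen on day 20 with an open wound has no healing time, so neither named test has a value to use. Yet the investigators know that healing took longer than 20 days, and they hold serial photographs of the wound. Unless a rule is supplied, that patient drops out and the analysis of all randomised patients becomes an analysis of those who were seen to heal.

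This matters if loss is related to healing speed. Visits continue only while the wound is open, so slow healers have the longest exposure to loss. Dressing frequency differs visibly between the arms, so unequal loss is plausible, although nothing in the article shows that it will occur. Removing slow healers from one arm makes that arm look faster than it is.

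A smaller point is that the primary test itself depends on whether the data look normal, and no criterion is given.

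**Working it through.** **1. The plan's own figure.** Inputs from the Sample size calculation section: difference 7 days, SD 7, 80% power, two-sided 5%, 10% attrition.

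- Normal approximation: n = 2 × (1.960 + 0.842)² × 7²/7² = 15.7, so 16 per arm.
- Two-sample t test (noncentral t): 16.7, so 17 per arm.
- Attrition: 17 / 0.90 = 18.9, so 19 per arm and 38 in total.

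The stated 38 is reproduced exactly. It is a t-test calculation for 2 × 17 = 34 observed healing times. Equivalently, 38 × 0.90 = 34.2, so about 4 patients are expected to have no value.

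**2. Loss unrelated to healing.** In simulation (19 per arm, normal healing times, SD 7, 10% lost at random), the completers' difference stays at about -7.0 days, the t test's type I error is about 5-6% and its power about 80%. There is no bias, and the power is the one planned.

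**3. Loss of slow healers from one arm (assumed).** If the slowest fraction p of an arm is lost, the mean of the remainder falls by SD × φ(z)/(1 - p), where z cuts off the upper fraction p.

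- 2 of 19: p = 0.105, z = 1.252, φ(z) = 0.182; shift = 7 × 0.182/0.895 = 1.4 days. Simulation gives 1.2 to 1.4, about 1.3, which is 1.3/7 = 19% of the target effect.
- 4 of 19, so that all the expected losses fall on one arm: p = 0.211, z = 0.805, φ(z) = 0.289; shift = 7 × 0.289/0.789 = 2.6 days. Simulation gives about 2.5.

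**4. Effect on the tests when the 2 slowest of 19 are lost.** The simulations use the set-up of step 2, mostly with healing rounded up to twice-weekly visits and 2,000 trials per scenario. The Monte Carlo standard error near 10% is √(0.10 × 0.90/2000) = 0.7 points, so small differences should not be read into.

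| Scenario | t, completers | Mann-Whitney, completers | Peto-Peto, lost patients censored |
|---|---|---|---|
| No true effect, 2 slowest NPWT patients lost: type I error | 9-11% | 8-10% | 4-6% if censored at the last visit before healing; about 7-8% if lost at day 14 or at a random time; about 9% if lost at day 7 |
| True 7-day effect, 2 slowest controls lost: power | 67-70% | 68-69% | 83% if censored at the last visit before healing; 69% if lost at day 7 |
| True 7-day effect, random 10% loss: power | 80% | 78% | 78-80% |

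With one slow NPWT patient lost, the t test's type I error is only about 6%. With four, it is about 21%.

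**5. Log-rank as the alternative.** Its type I error is 4.3% if the two patients are censored at the last visit before healing, but 11-14% if they leave early. Its power under random 10% loss is about 75-79%. On these assumptions Peto-Peto, which gives more weight to early healing times, is the better choice.

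**The case against.** The article fixes a population and families of tests; it does not say that patients without a healing date are dropped. A Mann-Whitney test can keep them by assigning the worst rank, and the handling of missing outcomes is often left to a fuller document. Follow-up runs until healing, which is expected at 19 to 26 days, so administrative censoring should be small. The 10% is a planning allowance and not a forecast that slow healers will leave.

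Much of this stands. A reader might infer that the named tests cannot include lost patients at all, or that the plan contradicts its own intention-to-treat promise. The text does not support either as a flat statement: a worst-rank rule would keep everyone, and no completers rule is written down. What remains is that the article does choose methods, that these need a healing time for every patient, and that its sample size is built on completers. A later document that censored lost patients would have to replace the named tests and not merely add detail.

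A reader might also infer that censoring removes the problem. It does not. Censoring assumes that loss carries no information about healing, which is what the harmful scenario violates. The favourable Peto-Peto results (type I error near 5%, power 83%) hold only when lost patients are followed almost until they heal.

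The choice between t and Mann-Whitney by distribution is common wording for all continuous endpoints. No numerical harm from it is shown here; it is a reason to name one test and nothing more.

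**Conclusion.** The concern holds as a mismatch between a time-to-event endpoint with expected loss and tests that need complete healing times, with no stated rule to bridge the two. The sample size of 38 is not in error.

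The size is conditional. Random loss does no harm beyond the power already allowed for. Loss of the 2 slowest of 19 from one arm shifts the difference by about 1.3 days and raises the type I error to about 8-11%; the same loss from the control arm lowers t-test power to about 70%. The loss pattern is an assumption, since the article gives only the 10%. It would go too far to say that the result will be biased or that the trial cannot be analysed validly. This is a point that should be fixed before analysis, not one that undermines the trial.

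**What to change.** Name one primary analysis in advance:

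- all randomised patients, by allocated arm;
- time from surgery to healing, with patients lost or still unhealed censored at their last wound assessment;
- Kaplan-Meier curves, with a Peto-Peto generalised Wilcoxon test as the single primary test;
- the difference in restricted mean healing time in days, with a 95% CI, at a truncation day fixed before analysis (the article gives no such day, so the sponsor must choose one).

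Add a Mann-Whitney analysis that gives lost patients the worst rank, as a sensitivity analysis for informative loss. It keeps everyone but treats every loss as a failure to heal, which is why it should not be primary. Keep the completers' t or Mann-Whitney result as supportive, and report the number, timing and arm of all losses.

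The cost is analysis wording; no new data are needed, since wounds are already assessed and photographed at every visit. Power falls by about 0-3 points under random loss, and the estimate becomes a restricted mean in place of a simple mean. If log-rank were preferred, the sample size would need rechecking, as its power may be nearer 75%.

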## Discussion

The primary objective of this RCT will be to evaluate the application of NPWT to PSC after stoma reversal regarding its effectiveness in reducing the wound-healing period.

Several mechanisms contribute to the efficacy of NPWT. NPWT reduces seroma formation in a wound and stimulates angiogenesis and granulation. Negative pressure also creates a hypoxic environment in a wound, resulting in the upregulation of inflammatory cytokines, which stimulates wound healing [10, 16].

One previous RCT evaluated the application of NPWT to laparotomy wounds following abdominal surgery [10]. In this previous study, the prophylactic use of NPWT reduced the SSI rate compared to that in the control group. However, the study did not compare the wound-healing period between the two groups. Two additional studies evaluated the application of NPWT to ileostomy closure sites and demonstrated the efficacy of NPWT in reducing the SSI rate [17, 18]. However, these previous studies focused on patients with primary linear closure of stoma wounds and did not evaluate the wound-healing period.

Uchino et al. [3] conducted an RCT with a similar primary endpoint to that in the present planned trial. The authors failed to demonstrate the efficacy of NPWT in significantly reducing the wound-healing period. However, the participants of this previous RCT comprised patients with ulcerative colitis, and the opening of the PSC was wider (8 mm) than that in the present planned trial (< 5 mm). As the opening of the PSC in the present planned trial will be ≤ 0.5 cm, we believe that our trial will more likely demonstrate positive results, which may be generalised to clinical practice. Another strength of our planned trial is that we will evaluate the cost of the wound dressings, number of wound dressings, and number of hospital visits for wound dressings after discharge, as direct and indirect assessments of the convenience level and medical cost.

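### Non-normal total dressing cost would go to a rank test, which does not compare mean cost per patient and can disagree with it if the arms' cost distributions differ in shape

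*Protocol article*

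**What the plan says.** The Endpoints section lists "total cost of wound dressings, and patient and observer scar assessment scale (POSAS) scores" among the secondary endpoints. The Discussion counts it as a strength of the trial that "we will evaluate the cost of the wound dressings", together with the numbers of dressings and hospital visits, "as direct and indirect assessments of the convenience level and medical cost".

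The Statistical analysis section states its scope as follows: "All analyses of the primary/secondary endpoints will be conducted with the intention-to-treat population". It then gives one pair of rules for continuous data:

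- "Normally distributed data will be examined using" Student's t test.
- "Non-normally distributed data will be examined using the" Mann–Whitney U test.

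Neither rule makes an exception for cost. The paragraph on dressing changes in the Interventions section sets daily changes in the control group and changes twice a week in the intervention group. It allows extra changes when a dressing is wet. It moves intervention patients who need more than one change a day in hospital to conventional dressings, because "NPWT dressing material is far more expensive than is conventional dressing material".

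**The concern.** The usual question about cost is whether the new dressing raises or lowers spending per patient. Only the arithmetic mean answers it, because mean cost times the number of patients gives total spend. Mann–Whitney asks something else: whether a patient drawn from one arm is more likely than not to cost less than a patient drawn from the other. It gives no estimate in money.

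The two questions have the same answer when the cost distributions differ only by a shift. They can part when one arm has a longer tail. That arm then has a lower median for the same mean, and the rank test leans towards calling it cheaper.

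Unequal shapes are plausible here. One arm uses costly units that are changed rarely, with a possible subgroup moved to cheaper material. The other uses cheap units that are changed daily. Slow healing or infection could lengthen the tail in either arm. The rule also lets the observed shape of the data decide which question is answered: means if the data look normal, ranks if not.

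**Working it through.** **1. The plan's own figure.** The Sample size calculation section assumes 19 ± 7 against 26 ± 7 days, 80% power, two-sided 5% and 10% attrition. The two-sample t calculation gives 16.7, so 17 per arm. 17 / 0.9 = 18.9, so 19 per arm and 38 in total. The stated 38 is reproduced, and nothing below affects it. No figure for cost is given.

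**2. Inputs for the cost check.**

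- n = 19 per arm (38 patients, 1:1), two-sided 5%: from the protocol article.
- Cost distribution: assumed lognormal, with true mean 100 in both arms.
- CV of cost: assumed, and shown as a range. The nearest anchor in the document is the spread of healing time, 7/26 = 0.27 and 7/19 = 0.37. Using it for cost assumes that cost accrues roughly in proportion to time to healing.

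**3. Formulas.** For mean m and CV c: σ² = ln(1 + c²), μ = ln(m) − σ²/2, median = m / √(1 + c²). The probability that a patient in arm Y costs less than one in arm X is Φ[(μ_X − μ_Y) / √(σ_X² + σ_Y²)]. Mann–Whitney responds to the distance of this probability from 0.5.

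Example with CVs 0.4 (X) and 1.0 (Y), both means 100:

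- σ_X² = ln 1.16 = 0.148 and σ_Y² = ln 2 = 0.693.
- Medians: 100/√1.16 = 92.8 and 100/√2 = 70.7.
- μ_X − μ_Y = (0.693 − 0.148)/2 = 0.272, and √(0.148 + 0.693) = 0.917.
- Probability = Φ(0.272/0.917) = Φ(0.297) = 0.617.

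Mean spend is identical, yet the more skewed arm is the cheaper one in about 62% of pairs.

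**4. Simulation.** 20,000 trials per row, equal true means, 19 per arm. Entries are the percentage of trials with p < 0.05.

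| CVs of the two arms | Mann–Whitney | Welch t |
|---|---|---|
| 0.5 and 0.5 (same shape) | about 5% | about 5% |
| 0.27 and 0.37 (healing-time spreads) | 5.6% | 5.0% |
| 0.27 and 0.5 | 9% | 6% |
| 0.5 and 1.0 | 17% | 7% |
| 0.3 and 0.8 | 20% | 7–8% |
| 0.4 and 1.0 | 24% | 8% |

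In the last three rows almost every Mann–Whitney rejection names the more skewed arm as cheaper.

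**5. When mean costs really differ.** At CVs 0.27 and 0.37, with the second arm's mean 1.5 times the first, Mann–Whitney rejects in 93% and Welch in 96%. At twice the mean, both reject in essentially all trials. The two tests then agree.

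**The case against.** The strongest reply concerns size. The article gives no cost data, and the only spreads it offers, those for healing time, produce almost no distortion (5.6% against a nominal 5%). Costs built from the stated dressing schedule, with normally distributed healing times and 0% to 30% assumed switching, show only slight skew, and both tests stay near 5%. The 17% to 24% figures need one arm at a CV of 0.8 to 1.0, which no number in the document supports. This objection stands, and it limits the point to a possibility of unknown size.

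A second reply is that the article never states a mean-cost objective. It presents cost beside dressing counts and visits as a general assessment, so the mean is a health-economic convention brought in by the reader. This stands in part. However, the Discussion says that the comparison is meant to inform on medical cost, and a rank test gives no amount of money.

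A third reply is that a condensed article may leave summary measures to the full protocol or analysis plan. That is true of detail such as reporting means by arm. The choice of test, however, is stated here, and it covers all endpoints.

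A reader might infer that the trial's cost conclusion would be unsupported, or that a false cost difference is likely. The documents support neither. Misleading results need mean costs that are close and shapes that differ strongly, and the article establishes neither condition.

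**Conclusion.** The point holds in a limited form. As written, non-normal total dressing cost would be tested by rank, and that test neither estimates nor tests a difference in mean spend per patient. Under the assumptions above (lognormal costs, equal means, 19 per arm), its rate of declaring a cost difference runs from about 5% to 6% at healing-time spreads, through 9% with moderately unequal spread, to 17% to 24% with strongly unequal spread. Which of these applies cannot be told from the document. One secondary endpoint is affected; the primary endpoint and the sample size of 38 are not. This is a minor improvement, worth making because it costs so little.

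**What to change.** Add one sentence to the Statistical analysis section: total cost of wound dressings will be compared between arms as the difference in arithmetic mean cost per patient in the intention-to-treat population, with a Welch 95% confidence interval, whatever the distribution; medians, ranges and any Mann–Whitney result are supplementary.

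A bias-corrected bootstrap interval is a natural alternative, but it does worse at this sample size. In simulation with equal means and 19 per arm, it excluded zero in about 9% to 12% of trials for the three strongly unequal CV pairs, and in about 8% when both CVs were 0.5. Welch gave 7% to 8% and about 5% respectively.

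The change costs one sentence and a few lines of code, with no extra patients or data. There are two downsides: the interval will be wide at 19 per arm, and Welch is itself slightly liberal (about 7% to 8%) under strong unequal skew.
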